### Data collection

#### Primary outcomes

Data regarding mental disorders will be collected through the Patient Health Questionnaire (PHQ) [53], a self-reported version of the PRIME-MD. We will use the subscales of the Díez-Quevedo et al.’s Spanish validated version [54] (except where indicated) to recruit participants and determine the severity of their emotional symptoms.

##### Depression symptoms

Participants will be evaluated using the 9-item PHQ subscale (PHQ-9) [55], which scores the 9 DSM-IV depression criteria present in the previous 2 weeks from 0 (*not at all*) to 3 (*nearly every day*). A score of 10 (at least 5 items rated with 2 [Item 9 also scores 1], and with Item 1 or 2 amongst them) is usually the cut-off point for major depression disorder (MDD): a score of 10–14 indicates minor depression, moderate MDD, or dysthymia; 15–19, moderately severe MDD; and 20–27, severe MDD. This tool has been tested in Spanish primary care centres (McDonald’s *ω* = .89) [56], when 10 was validated as the cut-off point for MDD screening (a sensitivity of 95% and a specificity of 67%).^1^

##### Anxiety symptoms

The 7-item Generalized Anxiety Disorder scale (GAD-7) [57] assesses common anxiety symptoms for the previous 2 weeks from 0 (*not at all*) to 3 (*nearly every day*). Cut points of 5, 10, and 15 represent mild, moderate, and severe anxiety, respectively. The algorithm sets 8 as the cut-off point for GAD, though it has been found that a score of 10 is more optimal [57]. We will use the version validated by García-Campayo et al. [58]. This was tested recently in primary care centres (Cronbach’s *α* = .83) [59], when 10 was confirmed as the best GAD screening criterion (a sensitivity of 87% and a specificity of 78%).

##### Panic symptoms

Since panic attacks can appear with any mental disorder (not just anxiety) [60], these symptoms should be measured separately. The Panic Disorder PHQ subscale (PHQ-PD) [61] is the specific panic disorder module of the PHQ and scores each DSM-IV criterion as *yes* or *no*. Muñoz-Navarro et al. [62] tested it in Spanish primary care settings and modified the original algorithm to increase the sensitivity for PD diagnosis: the most optimal cut-off point for screening purposes was 5 (the first item [for panic screening] and one of the following 3, plus 4 somatic symptoms; a sensitivity of 77% and a specificity of 72%).

##### Somatization

The 15-item PHQ subscale (PHQ-15) [63] is the somatization module of the PHQ. It scores symptoms present in the previous 4 weeks from 0 *(not bothered at all*) to 2 (*bothered a lot*). It includes 13 somatic symptoms plus 2 from the PHQ-9 (sleeping problems and fatigue); cut points 5, 10, and 15 represent low, medium, and high somatic symptom severity, respectively. However, whereas the original algorithm requires a score of at least 2 in 3 or more somatic symptoms to screen a somatization disorder (a sensitivity of 78% and a specificity of 71%) [64], the cut-off point usually used is 10, as it is in the PHQ-9 and the GAD-7 [65]; nevertheless, since this number can be obtained with 10 symptoms rated with the minimum severity, we decided to join both criteria. Furthermore, although an absence of biological cause is also often required (since PHQ-15 does not distinguish between medically explained and unexplained symptoms) [63], the self-administered nature of the PHQ-15 makes it difficult for the subject to determine this. This tool has been validated with Spanish psychiatric outpatients (*α* = .78) [66].

#### Secondary outcomes

##### Eating disorders and alcohol abuse

The PHQ can also be used to measure the presence of other mental disorders. The Spanish version [54] detects eating disorders such as bulimia nervosa or binge eating disorder (a sensitivity of 92% and a specificity of 98%) and alcohol abuse (a sensitivity of 76% and a specificity of 99%). Affirmative answers to Items 6a to 6c and 8 indicate bulimia nervosa; a negative answer (or no answer at all) for Item 8 points to a binge eating disorder. An affirmative answer to either Item 10a to 10e indicates alcohol abuse. In any of these cases, the patient would be interviewed by a clinical psychologist to confirm a possible diagnosis of eating, alcohol, or personality disorder.

##### Level of impairment

The Sheehan Disability Scale (SDS) [67] is a self-administered test that measures subjective symptom-related impairment with 5 11-point Likert items. The first 3 items rate key areas in the previous month: work, social life/leisure activities, and family life/home responsibilities. Two additional items assess stress level and perceived social support in the previous week. We will use the Spanish version developed by Bobes et al. [68] because it has shown good properties in primary care populations (*α* = .83) [69]. One, 4, and 7 are the cut points for mild, moderate, and high disability, respectively.

##### General quality of life

Psychological, physical, social, and environmental domains will be assessed through the 26 5-point Likert items of the World Health Organization Quality of Life Instrument-Brief (WHOQOL-BREF) [70], the abbreviated version of the 100-item WHOQOL (WHOQOL-100) [71]. The more the participant scores, the better quality of life. The WHOQOL has been validated in Spanish populations [72, 73] and has shown good psychometric properties (*α* > .7) in psychological, physical, and environmental domains, though its internal consistency in social domains has varied from .58 [73] to .75 [72].

##### Ruminative thinking

The 22-item Ruminative Responses Scale (RRS) [74] was originally developed to measure ruminative responses to depressed mood. It has been validated in a Spanish population [75]; however, only the 5-item brooding factor subscale (RRS-B) will be used in the proposed trial (*α* = .79) [76]. The RRS-B scores how often the participant thinks as described in each item (1 = *almost never* to 4 = *almost always*) when they are discouraged, sad, or depressed.

##### Worry

The Penn State Worry Questionnaire (PSWQ) [77] measures pathological worry as an uncontrollable and general state (i.e., as a GAD feature). It has been validated in Spain [78]. The proposed study will use an 8-item abbreviated version (PSWQ-A) [79] that has already shown good properties in primary care (*α* = .9) [76]. The PSWQ-A items rate how far worries affect the person (1 = *not at all typical of me* to 5 = *very typical of me*).

##### Attentional and interpretational biases

The Inventory of Cognitive Activity in Anxiety Disorders (IACTA) was originally developed by Cano-Vindel [80]. It includes several subscales that assess distortions according to Eysenck’s four-factor theory [81]. The 5-item, abbreviated panic version, the IACTA-Panic Brief (IACTA-PB; *α* = .87) [76] will be used to measure attentional biases. It scores how often the participant has certain cognitive distortions (0 = *almost never* to 4 = *almost always*). In addition, we will use the Questionnaire of Cognitive Distortions in Emotional Disorders (CDTE) [The PsicAP Group: Cuestionario de Distorsiones Cognitivas en Trastornos Emocionales, unpublished], an under-review tool that scores the frequency of certain cognitive biases in the main EDs (i.e., MDD, GAD, PD, and somatization disorder) from 0 (*almost never*) to 4 (*almost always*). It includes 16 items that measure the presence of four factors: sustained attention bias (*α* = .96); divided attention bias (*α* = .95); magnification interpretational bias (*α* = .94); and catastrophization interpretational bias (*α* = .96), with high levels of discriminant validity amongst the four EDs (ROC values > .8).

##### Emotion regulation strategies

The 36-item Cognitive Emotion Regulation Questionnaire (CERQ-36) [82] measures the specific cognitive emotion regulation strategies a person uses to face a stressful event. It scores how often the participant thinks as described (1 = *almost never* to 5 = almost always). The CERQ has been validated in a Spanish population [83]; the 18-item shortened version [84] will be used in the proposed study (*α* values range from .84 [*adaptive*] to .72 [*less adaptive*]).

##### Metacognitions

The 30-item Metacognitions Questionnaire (MCQ-30) [85] is a short version of the original MCQ [86], which measures beliefs about one’s own thinking processes. It has been validated in a Spanish population [87]. In the proposed trial, the 6-item *negative beliefs* (concerning uncontrollability/danger) subscale (MCQ-NB; *α* = .82) will be used [76]. This scores how far the patient agrees with the sentences presented to them (1 = *totally disagree* to 4 = *totally agree*).

##### Participant data and treatment satisfaction

An ad hoc questionnaire will be used to collect socio-demographic (gender, age, civil status, educative level, employment situation, and income level) and ED-related medical data (public and private health care consultations, accidents, medical tests, and sick leave in the previous 3 months, psychotropic drugs or other medications, and their posology). It includes an additional question about treatment satisfaction (at post-treatment and follow-ups). Medical records will be also consulted (though, for privacy reasons, only strictly necessary data will be collected).

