### Objectives and hypotheses

We believe that the implementation of transdiagnostic therapy at the primary level using a stepped-care model would save costs and reduce waiting lists. Mild to moderate cases could be treated in primary care and severe ones could be referred to specialized care for combined and more intensive therapies.

The proposed trial aims to compare, in terms of cost-effectiveness and cost-utility, a brief, transdiagnostic CBT in two different formats, individual and group, with the treatment ordinarily administered in primary care (treatment as usual [TAU]) for mild to moderate EDs (i.e., depressive, anxiety, and somatoform disorders). We expect that:

#### Hypothesis 1

Individual treatment will be generally as effective as group treatment in reducing emotional symptoms and cognitive-emotional regulation biases (i.e., both will show similar post-intervention size effects).

#### Hypothesis 2

The TAU will be the least effective (i.e., with significantly lower post-intervention size effects).

#### Hypothesis 3

The group therapy will return the best results in terms of cost-effectiveness and cost-utility.

#### Hypothesis 4

The TAU will have the least cost-effectiveness and cost-utility ratios.

#### Hypothesis 5

The same results will be found across the follow-up assessments (6 and 12 months after intervention).

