### Interventions

#### Group brief transdiagnostic cognitive-behavioural therapy (group tCBT)

It was developed by Cano-Vindel [43] and is based on the Unified Protocol for the Transdiagnostic Treatment of Emotional Disorders (UP) [44] and the IAPT programme [21]. It consists of seven 90-min sessions over 12–16 weeks and is conducted by a non-assessor clinical psychologist (hereafter the therapist), with 8–10 participants per group. Sessions are weekly or biweekly, and reduce in frequency as the intervention progresses; they are described below. (See Table 1 for the timeline.) The activities and homework are supported with materials such as theory documents, a CD for progressive muscle relaxation, self-recording sheets, and a therapy web. For more information, see González-Blanch et al. [43].

**Table 1 Tab1:** Group tCBT’s session timeline [43]

Therapy contents	Sessions						
	1	2	3	4	5	6	7
1. Psychoeducation	**×**	**×**					
2. Relaxation	**×**	**×**					
3. Cognitive restructuring			**×**	**×**	**×**	**×**	**×**
4. Behavioural techniques				**×**	**×**	**×**	**×**
5. Relapse prevention							**×**

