#### Treatment as usual (TAU)

Participants in this group will be provided with common primary care treatment by a GP in a face-to-face consultation that seldom lasts more than 10 min. TAU usually consists of pharmacological treatment, though it might also involve practical advice or even no treatment at all [51]. The first consultation will count as part of the recruitment process and, if the patient agrees to participate in the trial, no therapy will be provided until they are allocated to a group. Once in the TAU intervention, if the practitioner recommends psychological treatment (e.g., referral to specialized care), the participant would be excluded to avoid contamination between clusters. TAU does not comprise a specific number of sessions; it will end when the GP considers the patient recovered.

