#### Collection process

First, the 4-item PHQ ultra-brief subscale (PHQ-4) [91] will be used for the recruitment phase. The PHQ-4 gathers 2 items from the PHQ-2 and 2 from the GAD-2 (short versions of the PHQ-9 and GAD-7, respectively). It has been used in a Spanish primary care population (Spearman-Brown’s *ρ*_PHQ-4_ = .72; *ρ*_PHQ-2_ = .86; *ρ*_GAD-2_ = .76) [92]. A score greater than or equal to 3 would indicate the need for additional assessment (PHQ-2: a sensitivity of 90% and a specificity of 61%; GAD-2: a sensitivity of 88% and a specificity of 61%). It can be an extremely useful tool, as it helps to accelerate the screening process. It has been suggested, however, that both PHQ-2 and GAD-2 sum scores should be regarded separately in primary care samples [92]. The first item from the PHQ-PD has been added to screen panic disorder.

Second, depression, anxiety, panic, and somatizations will be assessed through the PHQ subscales mentioned above. If a participant scores as having a severe ED (depressive or anxiety disorder) or a non-emotional mental illness, or if the diagnosis is not clear, they will undergo a second evaluation with a gold-standard tool. The Structured Clinical Interview for DSM Axis-I Disorders (SCID-I) [93] will be used to assess panic and depression disorders and the Composite International Diagnostic Interview (CIDI) [94] will be used for GAD (since the former may not be adequate as it only includes one item for GAD). If these tools confirm the PHQ results, the patient will be referred to their GP, who will refer them to specialized care. The same will apply to those who score high in the SDS. All measures, except the PHQ-4, the SCID-I, the CIDI, and the treatment satisfaction question, will be collected at baseline, immediately after treatment, and 6 and 12 months later (see Table 2). Data will be also collected from medical records for the 3 months before participation in the study. To facilitate completion, the questionnaires may be answered in person, by email, online, or by phone.

To reduce the number of withdrawals, the clinical psychologists will telephone the participants to encourage them to continue with the treatment and/or to participate in the follow-up assessments. People who drop out of the intervention will still be invited to complete the questionnaires, especially at the first post-treatment assessment (immediately after the intervention).

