#### Cost analysis

Cost-related data will be collected through medical records and ad hoc questionnaires, from 3 months before inclusion in the study to 12 months after the intervention. Direct costs will be calculated by adding the ED-related costs due to medication use (antidepressants, anxiolytics, hypnotics, and sedatives), medical tests and other health services, and health personnel (primary/specialized care and public/private care). Medication costs will be calculated by multiplying price per milligram (€/mg) according to the Vademecum International (including VAT) [96] by the daily dose (mg) and the number of days of drug treatment. Cost data relating to medical tests and the use of health services will be obtained through the fee information published on the Andalusian Health Service’s official website [97]. Since a group psychotherapy session does not have a specific tariff, it will be considered as a GP consultation without medical tests because GPs and clinical psychologists have similar basic salaries [98]. Indirect costs will be calculated by multiplying the days of ED-related sick leave by the participant’s current daily minimum salary; the expense of replacement workers will also be factored in when incurred. Total costs will be obtained by summing direct and indirect costs.

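### The 3-month questionnaire recall leaves months 0–3 and 6–9 after treatment in no self-report window, although costs are claimed up to 12 months after the intervention

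*Protocol article*

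**What the plan says.** **Recall period.** Under Participant data and treatment satisfaction, the protocol article lists the questionnaire's service-use items as "public and private health care consultations, accidents, medical tests, and sick leave in the previous 3 months". Psychotropic drugs, other medications and posology follow as a separate item, outside the 3-month phrase. The same section says that medical records will be consulted too, limited for privacy to what is strictly necessary.

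**Timing.** Under Collection process, the measures "will be collected at baseline, immediately after treatment, and 6 and 12 months later". The Objectives and hypotheses section confirms that the follow-ups are counted from the end of treatment ("6 and 12 months after intervention").

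**Costing period.** Cost analysis names medical records and the ad hoc questionnaires as joint sources and gives one period for both: "from 3 months before inclusion in the study to 12 months after the intervention". Direct costs include private as well as public care.

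**Record extraction.** The only time frame that Collection process gives for records is this: "Data will be also collected from medical records for the 3 months before participation in the study".

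**Sick leave.** Cost analysis multiplies days of sick leave by a daily minimum salary and adds that "the expense of replacement workers will also be factored in when incurred".

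**The concern.** The recall period, the visit schedule and the costing period are all stated, and they do not fit together. After the end of treatment the visits are 6 months apart, but each questionnaire looks back only 3 months. Whatever is known only from the participant, private consultations above all, would go unrecorded for half of the post-treatment year. An analysis plan written later cannot recover answers to questions that were not asked.

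Cost is central here. The stated aim is cost-effectiveness and cost-utility, Hypotheses 3 and 4 rank the arms on them, and the incremental ratios are built from differences in mean total cost. Bootstrapping describes the sampling uncertainty of those differences; it does not restore costs that were never collected.

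The second, smaller matter is the valuation of sick leave. If a day of leave is given its salary value and the cost of a replacement is added for the same day, that day may enter indirect cost twice.

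**Working it through.** **Inputs**
- Recall window: 3 months (Participant data and treatment satisfaction).
- Visits: 0, T, T + 6 and T + 12 months, where T is the end of treatment (Collection process).
- T for group tCBT: "It consists of seven 90-min sessions over 12–16 weeks". At 365.25/12 = 30.44 days per month, 12 weeks = 84/30.44 = 2.76 months and 16 weeks = 112/30.44 = 3.68 months.
- T for TAU is not fixed: "it will end when the GP considers the patient recovered". No length in weeks is given for individual tCBT.
- Costing period: −3 to T + 12 months (Cost analysis).

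**Windows covered by the questionnaire**
- Baseline: −3 to 0, which matches the start of the costing period.
- End of treatment: T − 3 to T.
- First follow-up: T + 3 to T + 6.
- Second follow-up: T + 9 to T + 12.

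Uncovered: T to T + 3 and T + 6 to T + 9, which is 6 of the 12 post-treatment months, plus 0 to T − 3 when T exceeds 3 months.

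| | 12 weeks | 16 weeks |
|---|---|---|
| Months after inclusion, T + 12 | 14.76 | 15.68 |
| Covered | 2.76 + 3 + 3 = 8.76 | 3 + 3 + 3 = 9.00 |
| Uncovered | 6.00 | 6.68 |
| Share of time after inclusion | 6.00/14.76 = 41% | 6.68/15.68 = 43% |
| Share of whole costing period, T + 15 | 6.00/17.76 = 34% | 6.68/18.68 = 36% |

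The questionnaire alone therefore does not reproduce the stated costing period. If recall ran back to the previous assessment, the uncovered time would be 0 in both columns.

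**What records can add.** Cost analysis names records for the whole period. Participant data and treatment satisfaction mentions them without a time frame. Collection process gives a time frame only for the 3 months before entry. Reading the three together, records may supply public consultations and tests, and perhaps sick leave, after inclusion. No section says that they contain private consultations.

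**Sick leave.** Let S be the salary value of a day, R the replacement expense for a day, and r the share of sick-leave days that are replaced. If the two are added, the mean cost per day is S + rR; if each day is valued once, by salary, it is S. The documents give neither r nor R. Assuming R = S, the ratio is 1 + r, so r of 25%, 50% or 100% would raise indirect cost by 25%, 50% or 100%.

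**The case against.** The strongest reply is that records close the gap. One sentence in Cost analysis applies the full period to records and questionnaires alike, and the sentence in Collection process adds a pre-entry window without calling it the only one. This stands in large part: the 41–43% is a gap in one of two sources, not a share of costs lost. What it leaves is care known only by self-report. That may be modest, since public care is free (Background) and people in private therapy at entry are excluded (Eligibility criteria), but the documents give no figure.

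Three stronger readings are tempting and not supported.
- *Drug costs also fall in the gap.* Medication stands outside the 3-month phrase, and Cost analysis costs it by daily dose and days of treatment with no such limit.
- *TAU loses more follow-up than the other arms.* If TAU lasted 6, 9 or 12 months, the uncovered time would be 9, 12 or 15 months, but these lengths are assumptions. No section says that TAU courses are longer. Anticipated limitations acknowledges unequal durations, promises to consider them in the analyses, and commits to an effort to keep timings similar. The two post-treatment gaps are the same length in every arm, and nothing shows that costs differ most within them.
- *Replaced days are counted twice.* Adding the two amounts is the natural reading, but the text does not say how they are combined and fixes no cost perspective.

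It can also be said that the article is condensed and that the questionnaire itself and the timeline table are not visible. That would excuse silence, but the three periods at issue are stated.

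**Conclusion.** The point holds for self-reported service use. With a 3-month recall, months 0–3 and 6–9 after treatment lie in no questionnaire window, plus up to 0.7 month at the start of a 16-week course: 6.0–6.7 of 14.8–15.7 months after inclusion. The article claims costs for all of that time.

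The months rest on the group tCBT course length and on follow-ups timed from the end of treatment. The effect on total cost cannot be computed from the documents: it depends on how much private care is used and on whether sick leave is taken from records after inclusion. Private consultations are the clearest loss, because no other source is named for them.

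The sick-leave wording is a risk of double counting, not a demonstrated error, and a doubled day follows only if replacement pay equals the salary value.

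Both should be fixed. Neither shows that the cost comparison is invalid or biased towards an arm.

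**What to change.** 1. After baseline, change the recall line to the time since the last assessment. The cost is one changed line and somewhat more recall error over about 6 months.
2. Reconcile Participant data and treatment satisfaction, Collection process and Cost analysis so that record extraction runs from 3 months before inclusion to the last visit. State which items, sick leave in particular, come from records and which from the questionnaire.
3. The project started in September 2021, so some questionnaires may already have been collected with the 3-month recall. For items known only by self-report, scale the 3-month amount to its interval: 6/3 = 2 at each follow-up, and 3.68/3 = 1.23 at the end of a 16-week course. This assumes the same rate of use in the unasked months, so vary it in the sensitivity analysis already planned, for example from no use in the gap to the scaled amount.
4. State that each lost work day is valued once, by salary in the base case, with replacement cost only as an alternative in the sensitivity analysis. This costs one sentence.
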